### Ethics approval and indemnity

NHS Research Ethics Committee approval for the South Yorkshire Cohort protocol was obtained on 27^th ^April, 2010 (REC ref: 09/H1306/97).

### Consent

A core feature of the cmRCT design is 'patient centred informed consent' i.e. patient information and consent aim to replicate that of real world routine healthcare rather than conform to the needs of standard trial designs. Therefore all cohort patients consent to provide observational data at the outset, be contacted again, and for their information to be used to look at the benefit of healthcare treatments; however, consent to "try" a particular intervention in the future is sought only from those offered that intervention. This method of obtaining consent replicates the 'patient centred' information and consent procedures that exist in routine health care, where clinicians provide patients with the information they need, at the time they need it. In this study if patients provide all the following three consents (A, B and C) they are then regarded as members of the South Yorkshire Cohort.

• *A: *Health Questionnaire data to be used to *'help the NHS improve the long term health of people living in South Yorkshire'*. Information relating to this consent is provided in the GP Invitation letter to their patients (Additional File 2). Consent to provide this data is implicit and signalled by return of the Health Questionnaire to the researchers.

• *B: Further contact from the researchers*. This information is provided in the Invitation letter from the GP (Additional File 2) and consent is explicitly sought on the back page of the Health Questionnaire (Additional File 3).

• *C: *The information that patients provide to be used *'to look at the benefit of health treatments'*. Information relating to this consent is provided in the Invitation letter from GPs and is explicitly sought on the back page of the Health Questionnaire.

In addition to consents A, B and C, supplementary consent (D) is sought for:

• *D: *Access to *'your health records'*. Information relating to this consent is provided in the GP Invitation letter and on the back page of the Health Questionnaire.

Consent to the possibility of random selection to any future trial treatment is not sought. We suggest that it is unethical to falsely raise expectations of trial treatments when these expectations will not be fulfilled for the majority of the South Yorkshire Cohort study population. For example, if in the future 5 randomised controlled trials are embedded within the South Yorkshire Cohort (with for example 400 patients randomly selected to the intervention arm in each trial), this would equate to 2,000 out of 20,000 patients randomly selected to try an intervention and 18,000 not selected.

### South Yorkshire Cohort Guardian

Lack of consent to randomisation from individuals is not an insurmountable ethical issue for cluster randomised controlled trials [27]. For cluster randomised controlled trials, it is argued that the role of a Guardian is key to their ethical conduct [28]. Leeds East NHS Research Ethics Committee has effectively taken on the role of guardian of the South Yorkshire Cohort. All studies embedded or nested within the South Yorkshire Cohort (including randomised controlled trial) are required to obtain approval from Leeds East Research Ethics Committee. This will help ensure the safety and rights of South Yorkshire Cohort members and manage the risk of some groups being 'over researched'.

### Analysis plan

In order to ascertain the extent and type of any non response bias at the population level, the responders and non responders will be compared with regards to their GP practice and their postcode, sex and age. Initial analyses will be descriptive. Three different types of dataset will be produced according to the type of consent given:

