In order to inform NHS commissioning of obesity services, a range of information is required, namely, data from longitudinal observational studies and randomised controlled trials conducted in populations representative of the 'with need' population. Although the information is needed, few interventions or services currently benefit from this level of evidence. Existing longitudinal birth cohort studies provide long term outcome data on weight and chronic disease in the UK e.g. [5,6] and many other datasets provide data on adult weight and height in the UK, e.g. Health Survey for England [7], Quality Outcomes Framework [8], QResearch [9], however, none of these studies provide all the information required by the NHS. Birth cohorts only collect data on individuals born in that particular year/month, the annual home interviews of the Health Survey for England [7] collect cross sectional (not longitudinal) data, Quality Outcomes Framework [8] collects data opportunistically from those seeking treatment (and thus is unlikely to be representative of the general population), and QResearch [9] collects GP reported but not patient reported data. The South Yorkshire Cohort differs from these existing data sources in that it will provide an infrastructure which combines the strengths of the standard observational, longitudinal cohort study design coupled with a facility for multiple randomised controlled trials (see Figure 1). Additional qualitative and observational quantitative projects will also be able to be nested within this facility.

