### Study aims

The broad aims of the South Yorkshire Cohort are to:

• initiate a programme of research into the management and self-management of weight and long term conditions in adults in South Yorkshire

• to explore the relationship between key variables from an NHS perspective: long term chronic disease, weight change, quality of life, prescribed and over the counter medication, NHS and non NHS healthcare resource use and ethnicity and social class

• provide a cohort facility for multiple trials of interventions for the management and self- management of weight and long term chronic health conditions

• provide a research facility for longitudinal and qualitative studies in weight and long term conditions

The specific research objectives agreed as of 27^th ^June 2011 by the South Yorkshire Cohort Management Group are as follows:

1. To report the prevalence of long term health conditions and associated variables

2. To report the prevalence of obesity and overweight and associated variables

3. To describe the characteristics of weight management and self-management strategies self reported by the South Yorkshire adult population

4. To provide a detailed profile of the health and weight of underweight, normal weight, overweight, obese and morbidly obese patients registered with each participating GP practice, plus the types of services and treatments used by patients to manage their weight

5. To evaluate the clinical and cost effectiveness of potential weight management interventions for obese and overweight individuals and populations

6. To investigate the natural course of obesity and the effect of particular variables on health outcomes associated with obesity and its self-management

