### Study sample

The target population is all patients registered with GP practices in South Yorkshire aged 16 to 85 years. We use a two stage sampling method, which initially recruits GP practices and then recruits patients registered with these practices. Forty practices from South Yorkshire will be recruited and eligible patients are invited to participate in the South Yorkshire Cohort.

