#### Multiple Trials Facility

all completed returned Health Questionnaires (*Consent A*) with consent to be contacted again (*Consent B*) and consent for researchers to use the information they provide to look at the benefit of health treatments (*Consent C*).

For each dataset, analysis of key variables will be divided into six sections: height and weight will be used to calculate BMIs for all patients and for purposes of analysis patients will then be divided into six groups according to their reported BMI: underweight < 18.5, normal 18.5-24.9, overweight 25 -.29.9, obese 30 - 34.9, severely obese 35 - 39.9, morbidly obese 40 - 49.9.

The following types of NHS and non NHS healthcare resource use data will be analysed using descriptive statistics: medication (prescribed/self prescribed), hospital visits, contacts with other healthcare providers, and weight management strategies. Data will also be analysed in order to identify any interventions that may promote weight management. This will include cost effectiveness analysis and modelling of potential interventions (expected value of perfect information) to establish the potential need for further research. The burden of obesity in terms of economic costs will be estimated from a societal perspective. In order to make the results comparable with NICE guidelines [29], an NHS and Personal Social Services Prospective will also be undertaken, which will not include production loss. Resource use profiles will be used to calculate costs using national average unit costs from routine sources, e.g. NHS reference costs for inpatient resources [30]; Personal Social Services Research Unit costs of health and social care [31] such as GP visits, physiotherapy sessions. Costs of non-NHS interventions will be valued using market prices. Production losses will comprise lost employment and changes in employment as valued by the "New Earnings Survey". The EQ-5D will be analysed to provide estimates of Health Related Quality of Life.

Results will be compared with those reported in the following relevant studies [8, 10 and 25]. For those patients who consent to their NHS health records being searched then further analyses will be conducted using information on patients': chronic disease status: as recorded by GP including: diabetes, chronic obstructive pulmonary disease, stroke, coronary heart disease, cancer; NHS resource use: visits to NHS primary care healthcare professionals, visits to NHS secondary care.

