### Intellectual property and principles of collaboration

The South Yorkshire Cohort is assembling and observing longitudinally a cohort of NHS patients which will provide the following benefits:

• ongoing population surveillance of adults of all ages

• information on the natural history of the condition(s) and any associated factors

• information on 'treatment as usual'

• long term outcomes.

• longitudinal observational data

• a representative population based sample of adults of all ages

• up to date information to facilitate evaluation as well as hypothesis generation

• a multiple trials facility for hypothesis testing

• a recruitment facility for qualitative and quantitative research studies

Researchers with proposals to conduct randomised controlled trials embedded within the South Yorkshire Cohort or longitudinal observational research or use cohort data should read the guidance and conditions for studies utilising the South Yorkshire Cohort research facility and then complete the outline proforma available on the South Yorkshire Cohort website [http://clahrc-sy.nihr.ac.uk/south-yorkshire-cohort.html]. Proposals will be reviewed by the South Yorkshire Cohort Management Group. The principles for agreeing a proposal and releasing data are that the proposal (a) meets the broad aims of the South Yorkshire Cohort study, (b) is scientifically rigorous and practically feasible.

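### Prevalence is an objective and half or more of invitees are expected not to respond, yet no stated step carries the non-response comparison into the estimates, and two of three comparators are doubtful on the article's own account

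*Protocol article*

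**What the plan says.** Study aims, objective 2, is: "To report the prevalence of obesity and overweight and associated variables". Objective 1 is the same for long term conditions. The population to which these figures refer is given under Study sample: "The target population is all patients registered with GP practices in South Yorkshire aged 16 to 85 years". The sampling is described there too: "We use a two stage sampling method, which initially recruits GP practices and then recruits patients registered with these practices", and then "Forty practices from South Yorkshire will be recruited and eligible patients are invited to participate in the South Yorkshire Cohort". The Response rate section anticipates 45-50%.

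On non-response, the Analysis plan gives as its purpose finding out how much bias there is and of what kind. It says that the "responders and non responders will be compared with regards to their GP practice and their postcode, sex and age. Initial analyses will be descriptive".

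The external comparison is fixed at the end of the Analysis plan, under Multiple Trials Facility: "Results will be compared with those reported in the following relevant studies [8, 10 and 25". Reference 8 is the Quality Outcomes Framework, of which the Background says that it "collects data opportunistically from those seeking treatment (and thus is unlikely to be representative of the general population". Reference 10 is cited under Study design as the source of the cohort multiple RCT design. Reference 25 is a Sheffield population-based survey of 3,000 patients with 60% response.

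The section on intellectual property and collaboration lists among the benefits "a representative population based sample of adults of all ages".

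**The concern.** A descriptive prevalence from responders estimates prevalence among responders. It estimates population prevalence only if response is unrelated to the condition, or if the estimate is adjusted for what drives response. The plan intends to measure the difference between responders and non-responders on four variables and names no use for the result in objectives 1 and 2, or in the economic burden of obesity estimated from the same data.

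Sample size does not help. At about 20,000 the sampling error is so small that a modest responder/non-responder difference dominates the total error, and a narrow interval would suggest accuracy that is not there.

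The external comparison could give an independent check. As written, however, one source is a trial-design reference and another is one whose representativeness the article itself doubts. The national survey (reference 7) and the local obesity rates (reference 12), both cited in the article, are not on the list.

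**Working it through.** **The plan's own figures.** Sample size expects 4,400 obese and 400 morbidly obese adults among 20,000: 4,400/20,000 = 22%, or 4,800/20,000 = 24% if the groups are disjoint. Study setting gives 24% (men) and 25% (women) nationally, and locally Barnsley 28.4%, Doncaster 29%, Rotherham 27.6%, Sheffield 23.7%. No derivation of the expected yield is given, so it cannot be formally reproduced. The 24% is close to the national and Sheffield rates and below the other three. This says nothing about bias in data not yet analysed, but it shows the range of plausible true values: about 24% to 29%.

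**Inputs.** Response 45-50% (Response rate); n = 20,000 (Sample size); 40 practices (Study sample), so 20,000/40 = 500 per practice. Assumed, because the documents give no value: true obesity 27%, response of 40% and 47% by obesity status, ICC 0.005-0.02. The 20,000 are members of the trials facility, so the survey dataset, which needs fewer consents, would be at least as large.

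**Illustrative bias.** Observed prevalence = p·r₁ / (p·r₁ + (1−p)·r₀).
- p = 27%, r₁ = 40%, r₀ = 47%: 0.108 / (0.108 + 0.3431) = 0.108/0.4511 = 23.9%. Overall response is 45.1%, within the anticipated range. Bias is −3.1 points.
- Same response rates at p = 23.7%: 0.0948/0.4534 = 20.9%, bias −2.8. At p = 29%: 0.116/0.4497 = 25.8%, bias −3.2.

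**General form.** Bias = (1 − response) × (prevalence in responders − prevalence in non-responders). At 45-50% response, a gap of 2, 5 or 10 points gives a bias of 1.0-1.1, 2.5-2.75 or 5.0-5.5 points, with the sign of the gap.

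**Against sampling error.** Simple-random 95% half-width at p = 27%: 1.96·√(0.27 × 0.73/20,000) = 0.62 points. The gap that gives a bias this large is 0.62/0.55 = 1.1 to 0.62/0.50 = 1.2 points.

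**Clustering.** Design effect = 1 + 499 × ICC.

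| ICC (assumed) | Design effect | Half-width (points) |
|---|---|---|
| 0.005 | 3.5 | 1.15 |
| 0.01 | 6.0 | 1.51 |
| 0.02 | 11.0 | 2.04 |

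**Comparators, by how the article cites them.**

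| Reference | Role elsewhere in the article | Listed? |
|---|---|---|
| 8 | Quality Outcomes Framework; representativeness doubted in Background | Yes |
| 10 | Trial design and its comparative properties (Study design) | Yes |
| 25 | Sheffield population-based survey, 60% response | Yes |
| 7 | Health Survey for England | No |
| 12 | Local obesity rates (Study setting) | No |

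**The case against.** The strongest objection is that much of this argues from silence. The article is condensed, no analysis plan is shown, and the text speaks only of initial analyses. Weights and clustered standard errors are often left to the analysis plan. A reader might infer that the authors decided against correction or intended to ignore clustering. The text does not support that: it states no correction and no interval method, and rules out neither. This part of the objection stands and limits the claim.

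Other parts also stand. A reader might infer that the bias is known, or that it lowers obesity prevalence; the documents give no responder/non-responder gap, so both size and sign are open. A reader might take the practices to be a non-random sample; the Recruitment section gives only the means of contact and does not say how practices were chosen. A reader might think selection through the further consents is ignored; the plan defines three datasets by consent and analyses key variables, including BMI group, in each, which covers much of it.

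On comparators, the plan does not call the comparison a test of representativeness, and comparing with reference 8 is not an error in itself. Nor can it be said that reference 10 contains no usable data: the reference list is not shown, and the number may be a slip. What survives is that the list, as printed, does not fit the article's own description of its sources. An unseen analysis plan does not remove that inconsistency.

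**Conclusion.** The point holds in limited form and is worth acting on. The article sets population prevalence as an objective, expects 50-55% non-response, calls the sample representative, and states only a comparison that would measure bias without using it. Two of three named comparators need attention: one is probably a citation error, and one is usable only with the limits that the Background gives it. Reference 25 is sound, so it would be too strong to call the whole list wrong.

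The size is illustrative. A bias of about 3 points against a half-width of 0.6 (1.2-2.0 with clustering) rests on assumed response rates by obesity status and an assumed ICC. The firmer result is that a responder/non-responder gap of just over 1 point already matches the simple-random half-width. A reader might extend this to the trials run within the cohort; randomised comparisons there are not affected, because both arms come from the same responders.

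**What to change.** 1. In the Analysis plan, state that objectives 1 and 2 will be reported weighted for response, or calibrated to the practices' age, sex and postcode counts, beside the unweighted figure, with practice as the cluster for standard errors.
2. Check and correct reference 10 in the comparator list. Add references 7 and 12, age-sex standardised where their published detail allows. Keep 25. Use 8 only with its limits stated.
3. Qualify the claim of a representative sample, for example by making it conditional on the non-response results.

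**Cost.** No new data from patients. The variables are those the plan already intends to compare, but Recruitment says that the practices hold the identifiable lists, so non-responder counts must be obtained from them. Aggregate counts are enough for calibration. Intervals will be wider. Weights remove only the bias that these variables explain; in the illustration response depends on obesity itself, so part of that bias would remain. Practice counts also represent the 40 practices rather than the whole county, and the report should say so.

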#### Survey

all completed returned Health Questionnaires (*Consent A*).

#### Longitudinal observational study

all completed returned Health Questionnaires (*Consent A*) with consent to be contacted again (*Consent B*).

#### Multiple Trials Facility

all completed returned Health Questionnaires (*Consent A*) with consent to be contacted again (*Consent B*) and consent for researchers to use the information they provide to look at the benefit of health treatments (*Consent C*).

For each dataset, analysis of key variables will be divided into six sections: height and weight will be used to calculate BMIs for all patients and for purposes of analysis patients will then be divided into six groups according to their reported BMI: underweight < 18.5, normal 18.5-24.9, overweight 25 -.29.9, obese 30 - 34.9, severely obese 35 - 39.9, morbidly obese 40 - 49.9.

The following types of NHS and non NHS healthcare resource use data will be analysed using descriptive statistics: medication (prescribed/self prescribed), hospital visits, contacts with other healthcare providers, and weight management strategies. Data will also be analysed in order to identify any interventions that may promote weight management. This will include cost effectiveness analysis and modelling of potential interventions (expected value of perfect information) to establish the potential need for further research. The burden of obesity in terms of economic costs will be estimated from a societal perspective. In order to make the results comparable with NICE guidelines [29], an NHS and Personal Social Services Prospective will also be undertaken, which will not include production loss. Resource use profiles will be used to calculate costs using national average unit costs from routine sources, e.g. NHS reference costs for inpatient resources [30]; Personal Social Services Research Unit costs of health and social care [31] such as GP visits, physiotherapy sessions. Costs of non-NHS interventions will be valued using market prices. Production losses will comprise lost employment and changes in employment as valued by the "New Earnings Survey". The EQ-5D will be analysed to provide estimates of Health Related Quality of Life.

Results will be compared with those reported in the following relevant studies [8, 10 and 25]. For those patients who consent to their NHS health records being searched then further analyses will be conducted using information on patients': chronic disease status: as recorded by GP including: diabetes, chronic obstructive pulmonary disease, stroke, coronary heart disease, cancer; NHS resource use: visits to NHS primary care healthcare professionals, visits to NHS secondary care.

### Study management

The South Yorkshire Cohort is hosted within the Obesity Theme of the NIHR CLAHRC for South Yorkshire [3]. The Obesity Theme Advisory Group includes obesity commissioners from each of the four South Yorkshire NHS Primary Care Trusts, service providers, researchers from both Sheffield universities, clinicians and the public from across the region. This group provides an initial scientific review function and performs a gatekeeper and signposting role for internal and external enquiries for access to South Yorkshire Cohort data.

*South Yorkshire Cohort Management Group *has responsibility for overseeing the management of the study including: monitoring study progress and advising on modifications required, oversight of the study conduct, strategic planning, planning grant applications, co-ordinating embedded study applications, oversight of the budget, ensuring the study meets the requirements of Research Governance and data protection, dissemination of results.

*South Yorkshire Cohort Operation Group *is responsible for the day to day implementation of the study, including co-ordination of the staff working on the project, recruitment of GPs and patients, data management, and adherence to the protocol.

